### Study setting

This is a multi-centre, school-based study in 16 regions across the UK (figure 1). Students will be aged 16–19 years at time of enrolment, attending school or college year 12 (in England and Wales) or S5 (in Scotland), or their equivalent. This will include both government (local authority) and independent schools, sixth form colleges, single sex or coeducation schools, boarding or day schools. Study visits will be conducted in schools, although follow-up visits may occur in a community setting if participants have left school.

**Figure 1 F1:**
[figure not shown]
Study sites and vaccine group allocation

### Sample size

The sample size of 24 000 participants (8000 in each arm) is based on an estimated carriage rate 3.43% for genogroup B, C, W, Y or X in the Control Group at the 12-month swab. When assuming a retention rate of 80% and a design effect of 1.5, this sample size will provide 80% power to detect a 30% reduction of these genogroups combined, at a significance level of 0.05.

This anticipated carriage rate is based on results from the UKMenCar4 Study, which determined a carriage prevalence of 1.65% for genogroup B meningococcus, 2.3% for hyperinvasive meningococci and a combined prevalence of 4.2% for genogroup B, C, W, Y and X meningococci.^19^ The figure of 3.43% accounts for a potential 50% reduction in carriage of capsular groups W and Y due to the UK quadrivalent MenACWY vaccination programme; this figure is necessarily an estimate as there are limited data on the impact of the universal adolescent quadrivalent ACWY vaccine programme on carriage. A previous study in UK university students showed that immunisation with MenACWY-CRM reduced carriage of genogroup C, W or Y meningococci by 27.1% (95% CIs 6.9–42.9) and serogroup C, W or Y by 36.2% (95% CIs 15.6–51.7).^12^ A further UK university carriage cohort study suggested that the quadrivalent MenACWY vaccine exerts differential effects on capsular groups and did not prevent expansion of meningococci belonging to the hyperinvasive genogroup W clonal complex 11, although this was based on cross-sectional surveys rather than a longitudinal design.^21^

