### Randomisation, allocation and blinding

This is an open-label partially randomised study, with group allocation by study site. All schools within the geographical coverage area of each study site will be allocated to the same study arm, both for logistical reasons and because geographical allocation may increase the potential to detect any impact on herd protection. As a post-licensure study, blinded administration and/or placebo will not impact on the outcome of carriage prevalence and would introduce unnecessary cost and complexity to a trial of this scale. The allocation of initial sites was determined prior to the start of the study (figure 1). A capacity assessment stratified sites to either the control arm or immunisation sites depending on existing site expertise and the requirements to maintain equal numbers in each study arm. The immunisation sites were randomised to either the MenB-fHbp Group or the 4CMenB Group. Additional sites may be added during the study and will be pragmatically allocated to a study group to ensure balanced recruitment.

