### Patient and public involvement

This study will provide a unique opportunity to engage adolescents on an unprecedented scale to: (1) increase awareness of meningococcal disease; (2) highlight the importance of immunisation and (3) stimulate an interest in involvement in impact-driven research that potentially benefits the broader community. All year 12 (or equivalent) students at participating schools will attend assemblies, often involving meningitis survivors and disease-prevention advocates. These ‘meningitis ambassadors’ will discuss their personal experience of meningitis and provide education about signs and symptoms of meningitis. An ethically approved presentation will describe the science behind the study, including information about IMD and the link between vaccination, carriage and herd protection. Communication material used in this study will be developed with input from focus groups run by two meningitis charities, Meningitis Now and the Meningitis Research Foundation, who will also coordinate the provision of ‘meningitis ambassadors’. Other initiatives include a social media policy engaging students, schools and research teams with curated social media posts to complement public engagement aims. Combining these strategies will ensure that participants make a fully informed decision to participate in the study. Furthermore, by involving entire school year cohorts (regardless of enrolment into the study), an estimated 48 000 students across 200 schools will be engaged in a critical conversation about meningitis, research and the benefits of immunisation across the broader community. Study results will be submitted for publication in peer-reviewed journals, and then disseminated directly to the schools involved, as well as on the study social media platforms, and the Meningitis Now and Meningitis Research Foundation websites.

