### Statistical methods

A baseline analysis will occur after wave 2 when the study reaches approximately 50% enrolment. This descriptive analysis of baseline carriage rates will assess the validity of the prospective sample size calculation. There will be no interim analysis of vaccine impact. The principal analysis will be conducted using a modified intention to treat approach, including all participants who have had two throat swabs. Participants will be analysed according to allocated group, regardless of vaccine receipt. Based on previous UK school-based meningococcal carriage studies, the design effect was assumed to be 1.5 in the sample size calculations but will be calculated on the actual data collected.^24 25^

For the primary objective and each of the secondary objectives, carriage rates will be expressed as a mean with two-sided 95% Clopper-Pearson CIs for each group at baseline and at 12 months. The carriage rates in the MenB-fHbp and 4CMenB groups will be compared separately to the Control Group. The OR with two-sided 95% CIs will be calculated using logistic regression via a generalised estimating equations model using an exchangeable working correlation structure. Model covariates will include age, gender, season of recruitment and baseline carriage status a priori. Additional risk factors found to affect carriage at baseline will also be included. Gender and smoking (smoking, home smoking and vaping) are known to affect both vaccine-induced immune responses and meningococcal carriage, and these interactions will be reported regardless of significance. The level of statistical significance will be 0.05. There will be no imputation of missing data for the principal analysis.

Sensitivity analyses will be done for the primary and each of the secondary objectives and will include: analyses without adjustment or inclusion of covariates for completeness and to confirm the results from the primary analyses; a per-protocol analysis of participants who received both vaccine doses in the 4CMenB and MenB-fHbp groups; adjustment for the month of the outcome measure rather than season of recruitment to further investigate the potential effect of seasonality and multivariable imputation for missing data. All variables that will be included in the analysis model will be included in the imputation model and will assume data are missing at random.

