### Current study progress

At the time of writing 24 048 participants have been enrolled from over 120 schools across the UK. Assemblies raising awareness about meningitis, immunisation and research have reached over 40 000 students. In March 2020, study visits were temporarily suspended due to the SARS-CoV-2 pandemic and at this time, 11 170 participants had successfully completed the study. The protocol may require modifications to fulfil the study objectives.

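### The 80% power uses a design effect from school-based studies although whole regions are allocated, so it holds only if regions barely differ

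*Protocol article*

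**What the plan says.** The sample size "is based on an estimated carriage rate 3.43% for genogroup B, C, W, Y or X in the Control Group at the 12-month swab", with 8000 enrolled per arm. The Sample size section then states: "When assuming a retention rate of 80% and a design effect of 1.5, this sample size will provide 80% power". The full claim is "80% power to detect a 30% reduction of these genogroups combined, at a significance level of 0.05". Statistical methods gives the source of that design effect: "Based on previous UK school-based meningococcal carriage studies, the design effect was assumed to be 1.5 in the sample size calculations". The same paragraph adds that it will be recalculated on the trial data, without naming the level of clustering.

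Allocation is at a higher level. Randomisation, allocation and blinding states: "All schools within the geographical coverage area of each study site will be allocated to the same study arm". Study design gives 16 regions over three groups, and the Discussion contrasts this with another trial that randomised schools. The strengths and limitations box accepts that carriage is known to vary between sites and says the scale of the study will make up for it.

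**The concern.** A design effect depends on the size of the cluster and on the variation between clusters at the level that is allocated. A value suited to a school need not suit a region that contains many schools. Between-region variation enters the vaccine-control comparison in full and shrinks only with the number of regions, not with the number of students in each. The Sample size section makes no separate allowance for it, nor for the small number of regions behind each comparison.

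The trial is meant to inform immunisation policy. If the real power is well below 80%, a reader who relies on that figure would give a non-significant result more weight as evidence against a 30% reduction than it deserves.

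**Working it through.** **Inputs from the protocol article.** Control carriage p1 = 0.0343; 30% reduction, so p2 = 0.02401 and d = 0.01029; 8000 per arm; 80% retention, so 6400 analysed; design effect 1.5; 16 regions; three arms. For the test, "The level of statistical significance will be 0.05"; two-sided is taken from the two-sided confidence intervals.

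**Assumptions.** Regions are split evenly, 16/3 = 5.33 per arm, because the actual split is in a figure that is not shown. Between-region CVs of 0.10 and 0.20 are illustrative; the document gives none.

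**Step 1: reproduce the stated power.**
- Effective n per arm = 6400/1.5 = 4267.
- p1(1−p1) + p2(1−p2) = 0.05656.
- Variance of the difference = 0.05656/4267 = 1.326×10⁻⁵; SE = 0.003641.
- d/SE = 2.826. Power = Φ(2.826 − 1.96) = 80.7%. The stated 80% is confirmed.

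**Step 2: what a design effect of 1.5 implies at region level.**
- Analysed per region m = 6400/5.33 = 1200.
- From 1 + (m−1)×ICC = 1.5, ICC = 0.5/1199 = 0.00042.
- CV = √(ICC×(1−p1)/p1) = 0.108.
- So about 95% of regions would have to lie within 3.43% × (1 ± 1.96×0.108), or 2.7% to 4.2%, with no school clustering at all.

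**Step 3: add between-region variation to a school-level 1.5.** The added variance is CV²×(p1² + p2²)/5.33. The t columns use a noncentral t with ncp = d/SE. The df are 8 (5 v 5 regions, less 2), 10 (6 v 6, less 2) and 13 (16 regions less 3 groups). The SE is the same in every column.

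| Extra CV | Total variance | d/SE | Normal | t, df 8 | t, df 10 | t, df 13 |
|---|---|---|---|---|---|---|
| 0 | 1.326×10⁻⁵ | 2.83 | 81% | 70% | 72% | 74% |
| 0.10 | 1.654×10⁻⁵ | 2.53 | 72% | 60% | 63% | 65% |
| 0.20 | 2.640×10⁻⁵ | 2.00 | 52% | 42% | 44% | 46% |

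At control prevalence the total design effect, 1.5 + 1199×ICC, is about 1.9 at CV 0.10 and 3.2 at CV 0.20.

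**Step 4: does scale compensate?** At CV 0.20, let the number of students per region grow without limit. Only the regional term remains: 0.04×(p1² + p2²)/5.33 = 1.315×10⁻⁵, so d/SE = 2.84. Power is then 81% with a normal reference and 70-75% with t on 8 to 13 df. That regional term alone is as large as the whole variance assumed in Step 1.

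**The case against.** The strongest reply is that the figure is correct on its own inputs, and that the t reference is not in the document. The planned analysis is a GEE whose cluster unit the article may leave to the full protocol. That stands: 70-74% follows from region-level inference and not from the stated method. The normal-reference results (72% and 52%) do not depend on it.

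Second, school-based may describe where the earlier surveys were done and not the level at which 1.5 was estimated. The value may already contain some variation between areas, and adding a CV on top would then count it twice. This is fair, and it is why Step 2 treats 1.5 as a total. Even then the room is small: a CV of 0.10 alone uses 1 + 1199×0.000355 = 1.43 of the 1.5.

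Third, the plan has partial safeguards. A descriptive baseline analysis checks the sample size assumptions, the design effect will be recalculated, baseline carriage is a covariate and sites may be added. These could help, but none is tied to the region.

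Fourth, scale in the strengths box could mean many sites. More regions would indeed help, but there are 16, and the sentence draws no such distinction.

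Two stronger readings are tempting. A reader might infer that 70-74% is the most the design can deliver. The document does not support that: about 80% holds if regions do not differ beyond schools, and a smaller design effect or more sites would raise the t-based figures. A reader might also infer that clusters grew, since "students across 200 schools will be engaged in a critical conversation" while "participants have been enrolled from over 120 schools across the UK". The first is an outreach estimate that includes students not enrolled, and the second is a lower bound. Neither is a sample size input, so no power loss can be derived from them.

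**Conclusion.** The statement of 80% power is wrong as written, not in its arithmetic but in presenting as secured a figure whose design effect is not matched to the unit of allocation. Across the assumptions examined, power runs from about 80% (no regional variation beyond schools, normal reference) through 72% and 52% (extra CV 0.10 and 0.20, normal reference). With region-level t inference it is 70-74%, 60-65% and 42-46% at CV 0, 0.10 and 0.20. The conclusion rests on an even split of 16 regions and on assumed CVs. Which part of the range applies cannot be told from the document.

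**What to change.** Replace the flat 80% with power, or the detectable reduction, calculated with region as the allocated cluster over a stated range of between-region CV and with degrees of freedom that reflect the number of regions. State the level of clustering that the 1.5 represents. Estimate between-region and between-school ICCs from the baseline swabs already collected, and use them to place the trial within that range. Specify that the design effect to be calculated on the trial data is a region-level one. Correct the sentence in the strengths box: more students per region do not reduce variation between regions.

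The cost is revised wording and a short calculation on data already held. No extra participants are needed. The price is a less favourable power statement.

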### Study timeline

In order to meet recruitment targets and maximise the interval between immunisation and the final OPS within the structure of the school exam year, the study will recruit across 4 ‘waves’ over 20 months: wave 1 March–May 2018; wave 2 September–November 2018; wave 3 March–May 2019; wave 4 September–November 2019 (figure 2). The academic teaching year runs from September until April or May, depending on local jurisdictions. Recruitment will be balanced between study groups for each of the ‘Spring’ (March–May) and ‘Autumn’ (September–November) recruiting periods in view of expected seasonal variation in carriage. Completion of the final post-vaccination pharyngeal swab collection is expected in early 2021.

**Figure 2 F2:**
[figure not shown]
Study timeline by recruitment wave and year 12/S5 cohort (penultimate year of secondary school) at the time of enrolment. Vaccine groups receive either MenB-fHbp or 4CMenB at 0+6 months. See figure 3 for visit window ranges.

**Figure 3 F3:**
[figure not shown]
Study design

### Eligibility criteria

Participants will be healthy adolescents aged 16–19 years old at time of enrolment, in their penultimate year of participating secondary school or sixth form colleges, who intend to return for a further year of school. Students will be eligible for enrolment if they are willing and able to provide informed consent and meet the additional inclusion criteria:

Willing to comply with all study requirements.Consent for storage of oropharyngeal swabs and any bacterial isolates for future research.Willing to allow their general practitioner to be contacted to confirm vaccination status or medical history.

Participants will be ineligible to participate if they have received a course of either 4CMenB or MenB-fHbp in the past (by documentation or self-report). Furthermore, participants in the 4CMenB Group or MenB-fHbp Group will be ineligible if they meet any of the following criteria:

History of anaphylaxis to any component of 4CMenB or MenB-fHbp (For 4CMenB only, this includes allergy to latex).Any other significant disease or disorder, which in the opinion of the investigator may: put the participants at risk because of participation in the trial, influence the result of the trial or affect the participant’s ability to participate. Specific examples include haemophilia or medically diagnosed bleeding disorder, or receipt of anticoagulant medication, that prohibits the use of intramuscular injections.Known or suspected pregnancy.

Participants in the Control Group that fail any of the specific exclusion criteria 1, 2 or 3 will be eligible to participate in the assessment of carriage, but will not be able to receive the 4CMenB vaccine after the final OPS. Ineligibility arising during the trial due to criteria 1, 2 or 3 in the 4CMenB Group or MenB-fHbp Group will allow inclusion for assessment of carriage at the study endpoint but will exclude a participant from vaccination.

## Study procedures

### Recruitment

Recruitment will occur in participating schools; individual participants will not be directly recruited by the study teams outside of the school setting. Social media and the study website (www.beontheteam.uk) will be used for study information and awareness, but these platforms will not be used for recruitment. Participants will receive information through a school assembly about meningococcal disease and the study rationale and design. Subsequently, they will receive a written participant information sheet.

### Informed consent

All participants will be aged 16 years or over, and are therefore self-consenting as per the National Institute of Health Research guidelines.^22^ However, parents/guardians will be provided with information about the study via school communication platforms as well as directly by prospective participants. Consent will be taken by clinical staff (registered doctor or nurse) or non-clinical staff who have had appropriate experience and training. Where interested participants have vulnerabilities that may impair their capacity to provide informed consent, additional input or support from the individual’s parents/guardians will be sought. If there is ongoing doubt about an individual’s ability to provide informed consent, then they will not be enrolled in the study.

### Randomisation, allocation and blinding

This is an open-label partially randomised study, with group allocation by study site. All schools within the geographical coverage area of each study site will be allocated to the same study arm, both for logistical reasons and because geographical allocation may increase the potential to detect any impact on herd protection. As a post-licensure study, blinded administration and/or placebo will not impact on the outcome of carriage prevalence and would introduce unnecessary cost and complexity to a trial of this scale. The allocation of initial sites was determined prior to the start of the study (figure 1). A capacity assessment stratified sites to either the control arm or immunisation sites depending on existing site expertise and the requirements to maintain equal numbers in each study arm. The immunisation sites were randomised to either the MenB-fHbp Group or the 4CMenB Group. Additional sites may be added during the study and will be pragmatically allocated to a study group to ensure balanced recruitment.

### Interventions

All participants will be required to attend three study visits at their school (figure 3). Following informed consent, a baseline OPS will be taken by study staff using a standardised method of collection. A flocked swab will be used to sweep from one tonsil across the posterior pharynx to the contralateral tonsil. Participants in all groups will complete a brief questionnaire collecting demographic data and risk factors for meningococcal carriage such as smoking and antimicrobial use (see online supplemental file).^23^ The questionnaire is compatible with previous large-scale UK meningococcal carriage studies conducted in 1999, 2000, 2001 and 2014–2015, and the B Part of It Australian Study, which will allow an assessment of risk factors over time.^11 19 24 25^ The 4CMenB and MenB-fHbp groups will both receive a two-dose vaccine schedule at 0 and 6 months and all groups will have a second OPS taken at 12 months following enrolment. The Control Group will be offered a two-dose schedule of 4CMenB vaccination after their second OPS. Individual swab results will not be given to participants, in accordance with previous meningococcal carriage studies, however participants will be contacted confidentially if *N. gonorrhoeae* is detected.

10.1136/bmjopen-2020-037358.supp1Supplementary data

### Patient and public involvement

This study will provide a unique opportunity to engage adolescents on an unprecedented scale to: (1) increase awareness of meningococcal disease; (2) highlight the importance of immunisation and (3) stimulate an interest in involvement in impact-driven research that potentially benefits the broader community. All year 12 (or equivalent) students at participating schools will attend assemblies, often involving meningitis survivors and disease-prevention advocates. These ‘meningitis ambassadors’ will discuss their personal experience of meningitis and provide education about signs and symptoms of meningitis. An ethically approved presentation will describe the science behind the study, including information about IMD and the link between vaccination, carriage and herd protection. Communication material used in this study will be developed with input from focus groups run by two meningitis charities, Meningitis Now and the Meningitis Research Foundation, who will also coordinate the provision of ‘meningitis ambassadors’. Other initiatives include a social media policy engaging students, schools and research teams with curated social media posts to complement public engagement aims. Combining these strategies will ensure that participants make a fully informed decision to participate in the study. Furthermore, by involving entire school year cohorts (regardless of enrolment into the study), an estimated 48 000 students across 200 schools will be engaged in a critical conversation about meningitis, research and the benefits of immunisation across the broader community. Study results will be submitted for publication in peer-reviewed journals, and then disseminated directly to the schools involved, as well as on the study social media platforms, and the Meningitis Now and Meningitis Research Foundation websites.

